**Effects of home-based interval walking training on thigh muscle strength and aerobic capacity in female total hip arthroplasty patients: A randomized controlled pilot study**

**Protocol**

**Background**

Total hip arthroplasty (THA) is well-accepted surgical procedures in orthopedic with advanced arthritic disorders at hip joint.[1] Early targeted rehabilitation has been shown to reduce hospital length of stay without an increase in complication rates after THA.[2] However, it is well known that THA patients have significant muscular atrophy and weakness in the operated limb that can persist for at least 2 years[3,4] with mobility deficits remaining for a number of years.[1,5–8] Previous study has also indicated that muscle weakness of the operated hip is a major risk associated joint instability, prosthesis loosening, risk of fall, and other complications in THA patients.[9–12] Therefore, continual practice of exercise program is important for THA patients after hospital discharge, not only to prevent declining of muscle strength, but also to maintain a highly functional level and to prevent complications.

　Exercise programs such as muscle strengthening exercise and functional task have been shown to improve muscular strength, walking speed, and mobility in THA patients.[13,14] However, these programs are high cost, because they need to supervision of professional staff at hospital or rehabilitation center. In addition, some THA patients are excluded because difficulties with mobility and transport to a center preclude participation.^15, 16^ On the other hand, some researchers reported effect of home-based exercise program for THA patients without supervision.[15,16] However, these programs showed low adherence rate (50-70%). Therefore, we must develop a convenient and effective exercise program for THA patients.

Recently, we demonstrated that high-intensity interval walking training (IWT) consisting of 5 sets of fast walking above 70% peak aerobic capacity for walking (WVO_2peak_) for 3 min followed by 3 min of slow walking below 40% WVO_2peak_ per day more than 4 days/week for 5 months, increased WVO_2peak_ by ~10%, thigh muscle strength by ~10%.[17,18] In addition, the adherence to the IWT was very high (95%) in these studies. IWT is based on walking, and subjects can practice training at their home without supervision.

**Purpose**

- To examine the effectiveness to the physical function and psychosocial function of IWT on THA patients.
- To examine the safeness of IWT on THA patients.

We hypothesized that THA patients can practice the IWT in safety, and IWT will be improved physical function and psychosocial function in THA patients.

**Methods**

**Participants:**

Participants of this study will be recruited from the Department of Orthopedics, Hamamatsu University School of Medicine, University Hospital and patient advocacy group in Hamamatsu city. The inclusion criteria of participants were having undergone the primary THA before this study, and being able to walk independently. We do not consider using any assistive device. The exclusion criteria consisted of acetabular and/or femoral prosthesis failure and comorbidity such as cardiopulmonary, neurologic, or cognitive diseases. Participants will be randomly divided into control group or interval walking group. The randomization will be done by the one researcher, using a permuted block randomization (4 of block sizes).

**Tests:**

All assessments for subjects at the Hamamatsu University School of Medicine, University Hospital will be done at the department of rehabilitation. The assessments will be done before starting training (baseline), after 12 weeks (end of training),.

Isometric bilateral knee extension and flexion forces will be measured with an isometric dynamometer (GT-330; OG Giken, Tokyo, Japan). The higher value of 2 trials of extension and flexion forces, respectively.

WVO_2peak_ will be measured by previous reported methods using by tri-axial accelerometer (JD-Mate; Kissei Comtec, Matsumoto, Japan). [17,18]Subjects with JD-Mate on their back walked for 3 minutes on a flat floor at 3 graded subjective velocities: slow, moderate, and fast at ~25°C room temperature and ~60% relative humidity. At the same time, heart rate was counted with an electrocardiogram and 3-dimensional acceleration was measured at 10-millisecond intervals and recorded with 5-second memories as averaged values.[19,20] The total impulse from the accelerometer was transferred to a computer and converted to the oxygen consumption rate (VO_2_) using a previously reported equation.[19,20] WVO_2peak_ and peak heart rate (HR_peak_) for walking values are those for the last 30 seconds at maximal walking speed.

We will determine CVO_2AT_ at ~25°C room temperature and ~60% relative humidity with an expired gas analysis system (AE-310S; Minato, Tokyo, Japan). VO_2_ and carbon dioxide production (VCO_2_) were measured every breath. Exercise intensity was increased by 10 watts per minute and stopped when the anaerobic threshold was judged to have been reached according to the standard method,[21–23] by viewing the VO_2_ vs. VCO_2_ relationship displayed on the screen of the system during exercise. We also determined heart rate at CVO_2AT_ (HR_AT_).

Total energy expenditure for physical activity will be determined by summing the VO_2_ (O_2_ ml/kg/min) before (1 wk), during (12 wks), and after (1 wk) training periods, respectively, after excluding energy expenditure at rest, assuming that it was constant during these periods, and is presented as O_2_ ml/kg/wk. Walking steps will be determined by summing steps for the respective periods and are presented as steps/wk.

Hip joint pain will be evaluated with a scale of 100mm VAS, where 0 represents “no pain” and 100 represents “worst pain”.

Walking satisfaction will be evaluated using 0 as “no satisfaction” and 100 as “full satisfaction”.

The SF-36^®^ will be used to evaluate quality of daily life.[24,25]

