**Interval walking group:**

Subjects in IWT will be visited a gym near the hospital and received instructions about the exercise program. They will be told to repeat 5 or more sets of 2- to 3-minute low-intensity walking intervals at ~40% of the pre-training WVO_2peak_, followed by a 3-minute interval of high-intensity walking at >70% but <85% WVO_2peak_, >4 days/wk, so that total fast walking time per week reached >60 min. The intensity and steps were monitored with JD-Mate, worn on the mid-clavicular line of the right or left waist. A beeping signal alerted subjects when a change of intensity was scheduled, and another sound told them when their walking intensity had reached the target level every minute. Once subjects had learned the program, they were allowed to choose their training time each day. In addition, in IWT, energy expenditure by physical activity other than IWT and steps was measured with JD-Mate during the day, except for bathing and sleeping periods, while the beeping signal and sounds of the device were switched off.

Every 2 weeks, subjects will be visited the hospital, and data from the tracking devices will be transferred to a central server in the administrative center over the internet for automatic analysis and reporting based on the database on the effects of IWT in more than >3,000 middle-aged and older people with no THA, which we call the e-Health Promotion System (Kissei Comtec).[26] Physical therapists will use these reports to track daily walking intensity and other parameters given in **Table 2** to instruct subjects on how best to achieve the target levels. If the targets will be not met, they will encourage subjects to increase their efforts to achieve them.

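### The anaerobic threshold is judged live on screen and the ramp ends at that judgement, with no masked tester or masked later reading described, so 12-week CVO2AT and HR_AT are open to assessor bias

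*Protocol*

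**What the plan says.** The Tests section of the protocol describes the gas-exchange test as follows.

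- Load: "Exercise intensity was increased by 10 watts per minute".
- Data: VO2 and VCO2 "were measured every breath".
- End of test: exercise is "stopped when the anaerobic threshold was judged to have been reached according to the standard method", with three references cited for that method.
- Basis of the judgement: the VO2 versus VCO2 "relationship displayed on the screen of the system during exercise".
- A second outcome, HR_AT, is the heart rate at CVO2AT and so depends on the same threshold.

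On who does the testing, the same section gives only a place: assessments of subjects at the university hospital "will be done at the department of rehabilitation". The Participants section says "The randomization will be done by the one researcher", and the section on the interval walking group says "Physical therapists will use these reports to track daily walking intensity and other parameters". Neither the researcher nor the therapists are named as testers. The protocol does not mention masking of the tester, a second reader, or a determination made after the test.

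**The concern.** The protocol fixes a measurement rule in which one real-time visual decision does two jobs. It locates the threshold, and it sets how much data exist to check that location.

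The arms differ openly. One trains with an audible device and is coached every two weeks; the other is asked to keep its usual lifestyle. If the tester knows or learns the arm, an expectation of benefit could shift the 12-week call in one arm without any intent. Unlike random reading error, a shift that differs by arm biases the comparison between arms. Aerobic capacity is named in the trial's title, and CVO2AT is the aerobic outcome that rests on measured gas exchange; WVO2peak is converted from accelerometer output by an equation.

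**Working it through.** The protocol states no figure for this outcome (no expected change, SD or sample size), so there is nothing to reproduce. The check has two parts.

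**1. What a later reading could verify**

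- *Late call.* If the breath-by-breath traces are kept (storage is not stated), they contain points on both sides of the threshold. A later reader could find the threshold below the stopping point.
- *Early call.* Few or no points above the threshold are recorded. A change of slope cannot be confirmed, and a later reader cannot recover the missing stretch.

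The stopping rule therefore limits re-reading unevenly: late calls can be found, early calls cannot be corrected.

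Exposure also differs by visit. Baseline tests come before training starts, but the protocol does not say whether they come before allocation. If they do, they are less exposed. The 12-week tests necessarily follow allocation.

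**2. Sensitivity of the value to the timing of the call**

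This part applies only if CVO2AT is taken at or near the stop, which the protocol does not state.

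Input from the protocol: ramp of 10 W per minute, treated as a steady rise, so 30 seconds = 5 W and 60 seconds = 10 W.

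Assumed inputs, not in the protocol: oxygen cost of 9–11 ml O2/min per W; body weight of 50–60 kg; threshold of 11–15 ml/kg/min.

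Formulas: change in VO2 = oxygen cost × added load ÷ weight; relative change = change in VO2 ÷ threshold.

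| Delay | Added load | Smallest change | Largest change | Relative change |
|---|---|---|---|---|
| 30 s | 5 W | 9 × 5 ÷ 60 = 0.75 ml/kg/min | 11 × 5 ÷ 50 = 1.1 ml/kg/min | 0.75 ÷ 15 = 5% to 1.1 ÷ 11 = 10% |
| 60 s | 10 W | 9 × 10 ÷ 60 = 1.5 ml/kg/min | 11 × 10 ÷ 50 = 2.2 ml/kg/min | 1.5 ÷ 15 = 10% to 2.2 ÷ 11 = 20% |

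For orientation only, the Background reports a gain of about 10% in WVO2peak from earlier five-month programmes. That is a different measure over a longer period than this trial's 12 weeks, and the protocol gives no expected gain for CVO2AT.

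**The case against.** The best defence is that the call is a judgement against a cited standard method, not a free impression, and that the quoted sentence says when exercise stops, not that CVO2AT is the VO2 at that moment. If the threshold is read as the point where the VO2–VCO2 relationship changes, a later stop only adds points above it and need not raise the value. A tester who has seen the change on screen also has some points beyond it already. This stands, and it makes the percentages above conditional.

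A reader might infer four stronger things that the document does not support.

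- *That the tester is known to be unmasked.* The protocol is silent on who tests and what that person knows. The researcher who randomises and the coaching therapists would know the arm, but neither is said to test.
- *That the test cannot be re-read.* Gas exchange is measured at every breath, so the traces can be re-read up to the stop if they are kept. Only what lies beyond the stop is lost.
- *That the trial is biased by 5–20%.* This would need CVO2AT to be taken at the stop, the assumed conversion values, and a delay that differs systematically by arm. Nothing in the protocol shows such a delay, and error equal in both arms would not bias the contrast.
- *That this flaw undermines the trial's main evidence.* No outcome is named as primary, the title also names thigh strength, and this is a pilot.

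It could also be said that a later determination may be described elsewhere. The protocol itself, however, sets out the measurement procedure, and the only reading it describes is the live one.

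**Conclusion.** The point holds in a limited form. The protocol specifies a live, by-eye judgement that also ends the ramp, and it describes no masking of the tester and no masked determination later. With participants who cannot be masked, that leaves the 12-week CVO2AT and HR_AT open to assessor bias, and an early call would be hard to detect or correct.

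The size of any actual bias cannot be derived from the document. What can be said is conditional: if the value is taken at or near the stop, and under the assumed oxygen cost, weight and threshold, half a minute corresponds to roughly 5–10% of CVO2AT and a full minute to 10–20%. A less bias-prone reading is available from data that the test already produces, so this is a worthwhile, inexpensive improvement and not a fatal defect.

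**What to change.** In the Tests section:

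1. State that the on-screen call serves only to end the test.
2. State that the breath-by-breath files are kept.
3. Determine the analysed CVO2AT and HR_AT after the test with one fixed algorithm (for example V-slope), run on files coded without arm or visit.
4. Report, by arm and visit, how many tests give no determinable threshold.
5. Say who runs the test and whether that person knows the arm.

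The cost is some file processing by existing staff, and a few tests that were stopped too early may not be evaluable. The change does not remove the tester's influence on where the recording ends, which is why the count of indeterminable tests should be reported. Whether the ramp should run beyond the on-screen call affects how far patients are exercised and is left to the investigators.

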**Intervention**

**Control group:**

Subjects in CNT will be instructed to maintain the same lifestyle as before training. Every 2 weeks during the training period for IWT, they will be visited the hospital, and energy expenditure by daily physical activity and steps during the day, except for sleeping and bathing periods, will be transferred from the tracking devices to the central server in the administrative center over the internet but with no automatic analysis and reporting, unlike in IWT.

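### Energy expenditure and steps are fixed as plain period sums per week, so unworn daytime counts as inactivity and any difference in device wear distorts the activity contrasts

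*Protocol*

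**What the plan says.** The derivation is in the protocol under Methods, Tests. For energy expenditure: "Total energy expenditure for physical activity will be determined by summing the" oxygen uptake over three periods, which are given as "before (1 wk), during (12 wks), and after (1 wk) training periods, respectively". The resting component is then removed, as the protocol puts it "after excluding energy expenditure at rest, assuming that it was constant during these periods", with the result shown per kg and week. For steps: "Walking steps will be determined by summing steps for the respective periods and are presented as steps/wk".

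Both arms are to be monitored for the same part of the day. Under Control group, energy expenditure and "steps during the day, except for sleeping and bathing periods, will be transferred from the tracking devices to the central server", but "with no automatic analysis and reporting, unlike in IWT". Under Interval walking group, activity outside training "was measured with JD-Mate during the day, except for bathing and sleeping periods", with the device's signals switched off. Both arms come to the hospital every 2 weeks for data transfer.

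The arms differ in what the device does for them. In the interval walking arm it paces each session and signals when the target intensity is reached. Its data feed reports that physical therapists use to instruct participants and, if targets are missed, to encourage them. Controls only have their data uploaded.

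The protocol defines no valid day, minimum wear time or non-wear rule, and does not scale the totals to time worn.

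**The concern.** A sum over a calendar period measures activity correctly only if the device is worn for the same share of that period in everyone being compared. Here the resting component is removed, so an hour in a drawer and an hour in a chair both add nothing to net oxygen uptake and nothing to steps. The total mixes how active a participant was with how long the device was worn.

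The design gives the two arms different reasons to wear the device, so unequal wear is a foreseeable risk. The periods also differ in length (1, 12 and 1 weeks), and wear in a single week before training need not match average wear over the next 12.

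Two uses of the data are at stake. One is any comparison of overall activity between arms or periods. The other is the only objective check that controls followed the instruction not to change their lifestyle: lower wear during the 12 weeks could hide a real rise in their activity.

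**Working it through.** The protocol gives no wear figures and no expected activity level, so there is no stated number to reproduce. What follows is illustration. The 6,000 steps a day, the 9,000 on a training day and all wear levels are assumptions.

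**1. Equal true activity.** Let both arms take A steps a day, spread evenly, with the device worn d_I days a week in the interval walking arm and d_C in control. The plain sum records A × d_I and A × d_C, so

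apparent relative difference = d_I / d_C − 1.

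The same formula holds for shares of daytime hours worn.

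| Wear, interval walking vs control | Calculation | Apparent difference |
|---|---|---|
| 7 vs 7 days | 7/7 − 1 | 0 |
| 6.5 vs 6 days | 6.5/6 − 1 | +8.3% |
| 7 vs 6 days | 7/6 − 1 | +16.7% |
| 100% vs 90% of hours | 1/0.9 − 1 | +11.1% |
| 90% vs 80% of hours | 0.9/0.8 − 1 | +12.5% |
| 90% vs 100% of hours | 0.9/1 − 1 | −10.0% |

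At 6,000 steps a day, 6.5 vs 6 days gives 39,000 vs 36,000 steps/wk. The mean per worn day times 7 gives 42,000 in both arms.

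**2. Unequal true activity.** The wear ratio multiplies the true ratio:

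observed ratio = true ratio × (d_I / d_C).

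Take a true 54,000 vs 42,000 steps/wk, a ratio of 1.286 (+28.6%), with steps spread evenly over days. Wear of 7 vs 6 days shows 54,000 vs 36,000 (+50.0%). Wear of 6 vs 7 days shows 54,000 × 6/7 = 46,286 vs 42,000 (+10.2%). A real training effect is therefore inflated or diluted in the same way.

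**3. Change within the control arm.** If wear falls from 7 days in the week before training to an average of 6 during it, unchanged activity appears as 6/7 − 1 = −14.3%. A true rise of 16.7% would vanish: 1.167 × 6/7 = 1.00.

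**4. Does a mean per valid day repair this in the interval walking arm?** Only if day types are kept apart. Suppose 4 training days at 9,000 steps and 3 other days at 6,000: the true total is 36,000 + 18,000 = 54,000.

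- Device worn on the 4 training days only: the plain sum is 36,000 (−33%). The unstratified mean times 7 is 9,000 × 7 = 63,000 (+17%).
- Device worn on the 4 training days and 1 other day: the plain sum is 42,000 (−22%). The unstratified mean times 7 is 42,000/5 × 7 = 58,800 (+9%). Averaging by day type and weighting by the number of each gives 4 × 9,000 + 3 × 6,000 = 54,000 (0%).

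The simple mean is closer to the truth than the sum in both cases, but only the version by day type removes the error, and it needs at least one valid day of each type.

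**The case against.** The strongest reply is that valid-day thresholds and non-wear rules are data-handling detail that commonly sits in an SAP, which is not at hand here. The protocol also does not say outright that unworn days enter as zero, or that the 12-week sum is divided by 12 calendar weeks. That carries some weight, and a later rule could soften the problem. But the protocol does more than stay silent. It fixes the outcome as a period sum shown per week, and under that definition missing wear can only lower the value. A mean per valid day is a different definition, so this is a rule that needs changing as well as a gap that needs filling.

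A reader might infer that wear will be unequal, that it will fade over 12 weeks, and that the bias will favour interval walking. The documents do not support any of these. There are no wear data, the daytime wear scope is the same in both arms, and both attend every 2 weeks. The signals are off outside training, and the feedback concerns walking intensity and training targets, with no all-day wear target mentioned. Participants who need the device to train may still leave it off for the rest of the day, which would reverse the sign.

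Nor does the point reach the rest of the trial. Knee strength, the two aerobic capacity measures, pain, walking satisfaction and SF-36 are not computed from these sums. The protocol names no between-arm test of steps or energy expenditure and plans no check for compensatory inactivity.

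Finally, scaling by valid days can itself err when training and other days differ. That is correct, as the fourth step of the working shows, and it shapes the fix. It does not rescue the plain sum, which errs more in the same example.

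**Conclusion.** The point holds as a conditional one. The protocol's rule makes unworn daytime count as inactivity, so any difference in wear between arms or periods passes in full into the activity comparison as the ratio of wear: about 8% at 6.5 vs 6 days and 17% at 7 vs 6 days. Those wear levels are assumed. With equal wear the error is zero, and with lower wear in the interval walking arm it runs the other way. Different reasons to wear the device make unequal wear plausible; nothing in the protocol shows that it occurs or which arm it would favour.

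The reach is limited to energy expenditure, steps and the check on control lifestyle. It would be wrong to read this as a threat to the strength or aerobic capacity results. It is still worth changing, because the defect lies in a stated definition and the replacement is cheap.

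**What to change.** Replace the period sum for steps and energy expenditure by the mean per valid wear day times 7. Set the minimum daily wear time and the minimum number of valid days per week before the data are examined, and apply both identically in the two arms and all three periods.

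During training in the interval walking arm, average training days and non-training days separately and weight each by its actual number in the week. Require at least one valid day of each type where both occur.

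Report wear time by arm and period next to the activity results, and show the plain sum as a sensitivity analysis.

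The costs are small:

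- The main work is reprocessing device data.
- Some low-wear weeks become missing.
- Non-wear must be inferred from the device record. The protocol describes 5-second averaged records for the walking test, but does not say that the device logs wear or that daily-life data are kept at that resolution.
- The estimate assumes that unworn time resembles worn time of the same day type, which is why wear needs to be reported.
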